### 11.2.2 Secondary Efficacy Endpoints

The objectives of the analyses of the *secondary efficacy endpoints* are to:

- Evaluate descriptively and with model based estimation and informal hypothesis tests the effects of sildenafil therapy on sickle cell patients diagnosed with PH on multiple outcome measures including hemodynamic parameters, standard clinical measures of PH, and quality of life measurements
- Gain through descriptive and exploratory analyses a better understanding of what clinical and demographic factors might affect the efficacy of sildenafil for PH in this population

- Provide age and gender prevalence estimates for pulmonary hypertension in sickle cell patients

Secondary efficacy endpoints of the main trial will be analyzed as follows:

- Continuous outcome measures (e.g. hemodynamic parameters (RVSP), change in TRV, change in 6MW distance on sildenafil 20 mg vs. 40 mg and 80 mg in the group receiving active drug during the placebo controlled study) will generally be analyzed based on a combination of descriptive summaries and model-based analyses using models like that described for the primary endpoint analysis. At-visit-values and change from baseline values will be analyzed and reported. Descriptive, model based analyses will then be generated based on both analysis of variance type models (ANOVA) and analysis of covariance type models (ANCOVA) that control for both demographic and clinical parameters of interest (e.g. baseline NYHA/WHO functional class or baseline Borg dyspnea).
- Time to clinical deterioration of PH will be based on decisions of a blinded adjudication panel (see Section 9.2.4) and will be assessed by Kaplan-Meier methodology. These assessments will utilize log rank tests based on the Kaplan-Meier estimates used to test for differences between the two treatment groups. For this time to event outcome, Cox proportional hazards models will be used to assess whether clinical factors (e.g., TRV stratum, baseline NYHA/WHO functional class) act as confounders or effect modifiers of the treatment effect.
- The effect of treatment on the categorical measures of Borg dyspnea scale, BPI score, quality of life score, and NYHA/WHO functional class (all ordinal measures), will be examined descriptively. For each of these ordinal measures, both cross-sectional descriptions of the outcome at each time point and shift-tables from baseline will be developed to compare treatment arms descriptively. To generate informal hypothesis tests Mantel-Haenszel procedures will be used to assess for outcome differences at Week 16 and end-of-study controlling for baseline levels of the measure and TRV stratum.
- Differences across treatment groups for the clinical endpoints of death, episodes of acute chest syndrome, emergency department visits, outpatient/day hospital visits, hospitalizations, and transfusions will be analyzed using Fisher's exact test, if the number of events is sufficient. Otherwise, these data will be summarized by treatment group.

In the final report, all continuous efficacy measures (e.g. 6MW distance, hemodynamic parameters, quality of life assessments) will be summarized by N, mean, median, standard deviation, minimum, and maximum. Statistics used to summarize categorical variables (e.g. NYHA/WHO functional class) will include number and percent in each category. All efficacy measures will be summarized by treatment group, TRV strata, and treatment by TRV strata.

### **11.3 Safety Analyses**

All safety analyses will be performed using the ITT/SAF population. Safety variables will include laboratory variables and adverse event information. Specific endpoints that will be examined include:

- Incidence of AEs between baseline and Week 16
- Incidence of SAEs between baseline and Week 16
- Mortality incidence

The primary safety outcomes for the MIT will be all AEs; the subset of AEs defined as SAEs; and mortality. Treatment emergent AEs (those that begin or worsen after start of study drug), drug-related AEs, SAEs, and drug-related SAEs (as determined by the investigator) will be categorized by body system and MedDRA (Version 6.0 or later) preferred term.

The assessment of safety data will be based mainly on the tabulation of AEs, by TRV stratum and treatment arm. Additionally, AEs will be tabulated by severity and relationship to drug. Serious AEs will be described in detail. Comparisons across treatment groups, stratifying on TRV stratum will be made using a Cochran-Mantel-Haenszel chi-square test (or Fisher's Exact test as appropriate) on any AEs that occur in more than 10% of the subjects.

Additionally, continuous blood chemistry and hematology laboratory measurements will be categorized as normal/abnormal and summarized using shift tables, which describe changes in the values across visits.

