| Objectives:
Primary Objective(s):
In a randomized, double-blind, placebo-controlled phase II/III trial, to determine the efficacy of 16 weeks of sildenafil therapy on exercise capacity (six-minute walk distance).
Secondary Objectives: 
 
1. To determine the efficacy of 16 weeks of sildenafil therapy on echocardiographic estimates of right ventricular systolic pressure, and symptoms in patients with sickle cell disease and pulmonary hypertension, defined by tricuspid regurgitant velocity (TRV) <math>\geq 2.7</math> m/sec
 
2. Via a right heart catheterization in subjects with more severe pulmonary hypertension (TRV <math>\geq 3.0</math> m/sec stratum), to evaluate and compare the acute hemodynamic effects of inhaled nitric oxide and of oral sildenafil at rest in the catheterization laboratory and to determine the changes in hemodynamics after 16 weeks of sildenafil therapy
 
3. To determine the safety of 16 weeks of sildenafil therapy via adverse event reports and laboratory assessments
 
4. To evaluate prospective clinical outcomes in the subjects participating in the Observational Follow-up Study to the extent possible by each participating site
 
5. To provide subjects with open-label sildenafil for up to one year after completion of the Main Interventional Trial and to evaluate the long term safety of sildenafil in this population
 
 |

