Elevation in lactate dehydrogenase (LDH) is significantly associated with evidence of chronic hemolysis, including low levels of hemoglobin and haptoglobin, high levels of reticulocytes, bilirubin, plasma hemoglobin, and aspartate aminotransferase (AST). Elevated LDH levels also closely correlates with accelerated NO consumption by plasma, impaired vasodilatory response to NO donors, and is identified in patients with a syndrome of hemolysis-associated NO resistance, endothelial dysfunction and end-organ vasculopathy. This association has been confirmed in a longitudinal study of pulmonary hypertension in sickle cell disease patients. It has been suggested that LDH may be a simple but important biomarker for the clinical phenotype of pulmonary hypertension induced by chronic hemolysis.

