### 9.3.2 Clinical Laboratory Tests

Clinical laboratory tests (including the pregnancy test, if applicable) will be performed on blood samples collected at screening and all clinic visits for the Main Interventional Trial. Urinalysis laboratory tests will be performed on urine samples collected at screening and all clinic visits for the MIT as well. The following laboratory tests will be performed:

- Liver function tests (AST, ALT, albumin, total protein, total bilirubin, alkaline phosphatase)
- Renal function tests (potassium, sodium, chloride, bicarbonate, blood urea nitrogen (BUN), and creatinine)
- Mineral panel tests (magnesium, phosphate, calcium)
- CBC (Hemoglobin, hematocrit, RBC, MCHC, mean cell volume (MCV), reticulocyte counts, white blood cell (WBC) count, platelet count, and ANC)
- LDH
- INR values for subjects who are on vitamin K antagonists (e.g. warfarin)
- Activated Partial Thromboplastin Time (aPTT) for subjects who are on therapeutic doses of unfractionated heparin

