### **11.5 Statistical Considerations**

#### **11.5.1 Covariates**

The primary analyses will be conducted adjusting for baseline 6MW distance and TRV stratum, which is a stratification variable for the study design. Baseline laboratory measurements will be controlled for when analyzing laboratory outcomes. No other covariates will be used for adjustment in the primary analyses. For all model based secondary analyses, for which preliminary descriptive analyses provide evidence of a difference among treatment groups in a baseline demographic or clinical characteristic, these characteristics will be included in the models to assess whether they act as confounders or effect modifiers. If the estimate of the effect of the characteristic in the model is significant then it will remain in the model.

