### **13.2.3 Adverse Clinical Laboratory Trend**

An adverse clinical laboratory trend is a shift, in an adverse direction, in the mean (or median) change-from-baseline of a clinical laboratory parameter that is more adverse in

an active treatment group than in a control group (e.g., mean ALT change-from-baseline increases significantly more in the active treatment group than in the control group). An adverse clinical laboratory trend may also be evaluated via a "shift table," which cross-tabulates subjects' lab results (e.g., ALT values) in three categories (below normal range, within normal range, above normal range) at baseline, by their results in the same three categories post-baseline, separately for each treatment group. An adverse clinical laboratory trend would be demonstrated by increased frequencies of shifts in an adverse direction (e.g., above-normal ALT) in the active treatment group in comparison to the control group.

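### The one laboratory summary that section 11.3 names, a normal/abnormal shift table, hides direction and further worsening; low/normal/high tables plus change from baseline would be a cheap improvement

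*Protocol*

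**What the plan says.** The synopsis makes laboratory data part of a secondary objective: "To determine the safety of 16 weeks of sildenafil therapy via adverse event reports and laboratory assessments". Section 11.3 of the protocol lists laboratory variables among the safety variables and then ranks the outcomes: "The primary safety outcomes for the MIT will be all AEs; the subset of AEs defined as SAEs; and mortality". For laboratory data it names one summary: "continuous blood chemistry and hematology laboratory measurements will be categorized as normal/abnormal and summarized using shift tables". The sentence adds that the tables describe changes across visits. It does not mention treatment arm, direction or change from baseline.

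Three other places bear on the point:

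- Section 11.5.1, on covariates: "Baseline laboratory measurements will be controlled for when analyzing laboratory outcomes".
- Section 13.2.3 defines an adverse laboratory trend for safety reporting as "a shift, in an adverse direction, in the mean (or median) change-from-baseline of a clinical laboratory parameter" that is worse on active treatment than on control. It allows, as a further option, a shift table "in three categories (below normal range, within normal range, above normal range".
- Section 13.8.3 and Table 12 put that definition to work. Every six months the data coordinating center analyses change from baseline for each laboratory test, active against control, and reports to the DSMB.

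On collection, section 9.3.2 says: "Clinical laboratory tests (including the pregnancy test, if applicable) will be performed on blood samples collected at screening and all clinic visits" of the main trial. Its list includes hemoglobin, reticulocyte count, total bilirubin, AST and LDH.

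**The concern.** A normal/abnormal shift table is informative when most subjects start inside the reference range and can leave it in only one direction that matters. Neither condition is safe to assume here. Section 2.2 ties raised LDH in sickle cell disease to chronic hemolysis, with "low levels of hemoglobin and haptoglobin, high levels of reticulocytes, bilirubin, plasma hemoglobin, and aspartate aminotransferase (AST". Many subjects may therefore enter already out of range on the tests most relevant to their disease. If hemoglobin is low at baseline and falls further on treatment, the subject is abnormal before and abnormal after, and the table shows no shift.

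At stake is how informative the final laboratory safety summary is. The primary analysis, alpha and sample size are not affected. The protocol reports no hematologic laboratory signal for sildenafil, and none is suggested here.

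**Working it through.** **1. What the coding loses.** A below/within/above-normal table at baseline and follow-up has 3 × 3 = 9 cells, of which 9 − 3 = 6 are shifts. Collapse it to normal/abnormal:

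| Shift in the three-category table | Where it goes in the two-category table |
|---|---|
| below to above, above to below (2 cells) | abnormal to abnormal: no shift shown |
| within to below, within to above (2 cells) | normal to abnormal: direction lost |
| below to within, above to within (2 cells) | abnormal to normal: direction lost |

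So 2 of the 6 shifts disappear and the other 4 merge into 2 cells without direction.

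**2. What three categories do not cure.** A low value that falls further goes from below to below, which is on the diagonal of either table. Only change from baseline shows it. That is why the fix needs both parts.

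**3. Illustration of size.** The plan gives no figure to reproduce, and it does not state what share of subjects is normal at baseline. The inputs below are assumptions, except for the sample size.

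- Subjects per arm: 60, the evaluable number in section 11.6 before the 10% allowance (66 randomized).
- Baseline and follow-up: bivariate normal, unit variance, correlation r = 0.5, 0.7 or 0.9; SD of change = √(2(1 − r)).
- One-sided reference limit, set so that a share q is normal at baseline.
- Mean worsening on sildenafil: 0.5 SD of change; none on placebo.

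Expected normal-to-abnormal count per arm = 60 × P(baseline normal, follow-up abnormal).

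| q | Placebo to sildenafil, r = 0.7 | Excess at r = 0.5 / 0.7 / 0.9 |
|---|---|---|
| 10% | 3.2 to 4.3 | 1.0 / 1.1 / 1.0 |
| 25% | 6.0 to 8.9 | 3.1 / 2.9 / 2.1 |
| 50% | 7.6 to 12.8 | 6.4 / 5.2 / 3.1 |
| 75% | 6.0 to 11.6 | 7.6 / 5.6 / 3.0 |

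The fewer subjects start in range, the less this cell shows: about 1 extra subject at 10% normal, against 3 to 8 at 75%. The count covers that cell alone; returns from abnormal to normal would also be somewhat fewer on sildenafil.

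A difference in mean change uses every evaluable subject. Its 95% CI half-width, in units of the SD of change, is t(0.975, 118) × √(2/60) = 1.980 × 0.1826 = 0.36. With 66 per arm it is 0.34. Neither figure depends on q, and neither counts any gain from adjusting for baseline.

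**The case against.** The best case for leaving the text alone has four parts.

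*Nothing is contradicted.* A reader might infer that 11.3 conflicts with 13.2.3, because one uses two categories and the other three plus mean change. The documents do not support that. Section 13.2.3 defines a term used in the DSMB alert procedure, 11.3 does not use the term, and the three-category table is only an option there. Nor does 11.3 conflict with 11.5.1. The baseline-control statement belongs to the same chapter and applies generally, so 11.3 need not repeat it. This objection stands in full.

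*The DSMB already sees change from baseline.* This also stands. A reader might answer that the alert limit of p < 0.005 is too strict to help, since with 60 per arm a true difference of 0.5 SD would cross it only about 55% of the time. That figure is the chance of an alert at one look. Under 13.8.3 the results go into every semi-annual report whether or not the limit is crossed, so the argument fails. These reports are monitoring documents, however, and the protocol does not say that their laboratory analyses will appear in the final report.

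*Other data would catch real harm.* An adverse event under 13.2.1 can be an abnormal laboratory finding that worsened, and 11.2.2 compares transfusions between arms if events suffice. Both hold, and they lower the weight.

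*The statistical analysis plan may add detail.* It may, and 11.3 does not exclude further summaries. The point therefore does not rest on what 11.3 omits. It rests on the method that 11.3 does fix, a coding that discards information in the measured values.

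**Conclusion.** The two-category shift table is a weak choice for the only laboratory summary that 11.3 states. The loss of direction follows from the coding alone and needs no assumption. The masking of further worsening matters to the extent that subjects start out of range. Section 2.2 makes that likely for hemoglobin, reticulocytes, bilirubin, LDH and AST, but no share is given, so the counts above are illustration only and do not show a failure in this trial.

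The weight is low and no trial decision depends on it. Readings that go further, such as an internal contradiction, inadequate DSMB laboratory monitoring or an undetected sildenafil effect on blood counts, are not supported by the protocol.

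**What to change.** In section 11.3, replace the normal/abnormal coding with shift tables by treatment arm using below, within and above the normal range. Add one sentence: for continuous chemistry and hematology values, change from baseline to each visit will be summarized by arm, with the between-arm difference adjusted for the baseline value as 11.5.1 states, given with a 95% CI and presented descriptively.

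The cost is one or two sentences and a few more tables. No new data are needed, because the tests are already drawn at baseline and at weeks 6, 10 and 16, and the coordinating center already plans change-from-baseline analyses for the DSMB.

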### **11.4 Interim Analyses**

No formal interim analyses will be performed in this study.

### **11.5 Statistical Considerations**

#### **11.5.1 Covariates**

The primary analyses will be conducted adjusting for baseline 6MW distance and TRV stratum, which is a stratification variable for the study design. Baseline laboratory measurements will be controlled for when analyzing laboratory outcomes. No other covariates will be used for adjustment in the primary analyses. For all model based secondary analyses, for which preliminary descriptive analyses provide evidence of a difference among treatment groups in a baseline demographic or clinical characteristic, these characteristics will be included in the models to assess whether they act as confounders or effect modifiers. If the estimate of the effect of the characteristic in the model is significant then it will remain in the model.

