## 6 RANDOMIZATION AND BLINDING

The study will randomize 132 subjects.

After successful qualification of their baseline data and the completion of the RHC procedure (for subjects with TRV  $\geq 3.0$ ), subjects will be randomized to one of two treatment arms by the internet based, secure RhoRAND™ system provided by the Data Coordinating Center (DCC). Subjects in Arm 1 will receive sildenafil. Subjects in Arm 2 will receive oral placebo. A computer-generated, adaptive randomization schema will be used to allocate subjects 1:1 between the two treatment arms. Randomization will be stratified by site and TRV stratum ( $2.7 \text{ m/s} \leq \text{TRV} < 3.0 \text{ m/s}$  versus  $\text{TRV} \geq 3.0 \text{ m/s}$ ). As the number of stratification factors is rather large ( $9 \times 2 \times 2$ ), many strata may have fewer subjects than the block size, and a good balance can no longer be guaranteed for all of them^34. As a result, the use of a traditional stratified, blocked randomization schedule could lead to significant imbalance in treatment allocations, both across the study and within the various strata. In order to increase the likelihood of balance in treatment allocations, subjects will be randomized using the standardized range variation of the sequential allocation algorithm of Pocock and Simon, a minimization method. This method attempts to achieve treatment balance on several subject characteristics (i.e., site and TRV stratum in this study) simultaneously – not within separate strata. Minimization

consists of biasing the treatment allocation so as to minimize the total imbalance between the treatment groups on some scale. The order of entry of the subjects to the various sites and in the various prognostic groups is assumed to be random. As minimization is a dynamic method that uses information on subjects already entered to allocate treatment to the next subject, and thus a continuous updating of the information related to previous treatment allocations is required, a centralized randomization system will be used.

The unmasked statistician will monitor the balance of treatment assignments across subjects on anticoagulants (defined as vitamin K antagonists and heparin). If a significant imbalance is detected, anticoagulant use will be added as stratification factor in the randomization.

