- A single two-sample Wilcoxon rank-sum test (the nonparametric alternative to the two-sample t-test) to compare the change from baseline to Week 16 in the sildenafil arm to the change from baseline to Week 16 in the placebo arm for the 6MW distance. For those subjects with missing Week 16 measurements, these measurements will be imputed using a last observation carried forward (LOCF) approach or by using the last possible measurement (see section 11.5.5).
- An Analysis of Variance (ANOVA) model which is a small deviation from the t-test approach and the ANCOVA model. This method will use the change from baseline to Week 16 with missing values imputed by LOCF or by using the last possible measurement (see section 11.5.5), as the primary endpoint. The analysis will be based on a cell-mean model with the four treatment-by-TRV-strata groups as the cells. The primary hypothesis will be based on a test that the average change across the two strata differs between the two treatment groups. The hypothesis will be tested with an F-test with 1 numerator and N-4 denominator degrees of freedom, where N is the number of subjects in the ITT population.
- A linear mixed model, which will incorporate the 6MW measurements from the baseline, Week 6, Week 10, and Week 16 assessments. This model allows for comparison of the 6MW distance over the two treatment groups, controlling for time, TRV stratum, and baseline 6MW distance as fixed effects and subject as a random effect. This analysis uses likelihood-based estimation, and subject-specific effects and correlations between the repeated measurements are modeled via the within-subject error correlation structure. All available data will be used to compensate for the data missing on a particular subject.

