### 11.5.3 Multiple Comparisons and Multiplicity

The primary formal hypothesis test will be conducted using an alpha on a two-sided test of 0.05. Because only a single hypothesis test will be tested and other reported p-values will be considered descriptive, no adjustment for multiple comparisons will be made. Informal hypothesis tests conducted as a part of secondary analyses will all be two-sided tests, and the p-values from these tests will be presented as descriptive measures of strength of evidence. These descriptive p-values will be presented for differences between treatment groups in summary tables for secondary exploratory analyses.

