## 11.6 Sample Size

This study will randomize 132 subjects (66 to sildenafil and 66 to placebo). Sample size was determined based on the following considerations.

The measurement of primary interest is the change in 6MW distance from baseline to week 16. To estimate the trial sample size for the primary endpoint, we used data from Ghofrani's evaluation of the effects of sildenafil in subjects with chronic thromboembolic pulmonary hypertension. Ghofrani's study showed an average change from baseline of 53.7m in 6MW distance with a standard deviation of 67m after approximately 6 months of sildenafil treatment.

A t-test was used to compare the difference in change from baseline 6MW distance between the sildenafil and placebo treatment groups. In order to calculate the sample size the following assumptions were made:

- No subjects discontinue because of clinical worsening or death
- No subjects dropout prior to week 10 for other reasons
- Sixteen-week change in 6MW distance is normally distributed in both treatment groups
- Sixteen-week change in 6MW distance is 40m in subjects on sildenafil and there is no change in subjects on placebo (i.e., a difference of 40m between the two treatment groups)
- Standard deviation of change from baseline between 62 and 72m for the 16-week change in each of the treatment groups
- Power ranges from 80% to 90%
- Two-sided t-test with  $\alpha=0.05$

Table 6 presents the number of subjects needed per treatment arm for the range of assumed standard deviations and powers, thus the total number is 2 times the numbers presented in each cell.

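### Site is a minimisation factor but is barred from the primary ANCOVA, which is conservative if site is prognostic; secondary-model covariates are chosen from the data

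*Protocol*

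**What the plan says.** **Allocation.** Protocol section 6: "Randomization will be stratified by site and TRV stratum". The method is minimisation, which balances the two factors marginally and not within each site-by-TRV cell. Anticoagulant use may become a further factor if the unmasked statistician sees an imbalance. Section 11.5.2 expects about 9 sites.

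**Primary analysis.** Sections 11.2.1 and 11.5.1 specify an ANCOVA on the 16-week change with baseline 6MW and TRV stratum. Section 11.5.1 notes that TRV stratum is a stratification variable of the design, then adds: "No other covariates will be used for adjustment in the primary analyses". Section 11.5.2 treats site descriptively only.

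**Sensitivity analyses of the primary endpoint (11.2.1).** The rank test is "A single two-sample Wilcoxon rank-sum test" on change from baseline, with no stratification. The ANOVA and the mixed model beside it both include TRV stratum. None includes site.

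**Secondary models.** Under section 11.5.1, a baseline characteristic enters when descriptive analyses suggest that the arms differ on it. Then: "If the estimate of the effect of the characteristic in the model is significant then it will remain in the model". No threshold and no candidate list are given. Section 11.5.3 makes all p-values other than the primary one descriptive.

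**The concern.** Balancing arms on a prognostic factor removes that factor from the sampling variation of the treatment difference. If the model then omits the factor, its variance stays in the residual. The standard error describes a less balanced trial than the one run, so the test is conservative and the interval too wide. The plan handles this correctly for TRV stratum and not for site, and gives no reason for the difference. Because the exclusion is explicit, a SAP could not add site without contradicting the protocol. The same sentence would keep out anticoagulant use even if it were added to the minimisation.

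The secondary-model rule is a separate matter. Baseline differences after random allocation arise by chance. Selecting covariates on them, and then on their significance, means the model is not known until the data are seen, and the reported standard errors take no account of the selection.

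**Working it through.** **Inputs from the protocol.** Two-sided alpha 0.05 (11.5.3: "The primary formal hypothesis test will be conducted using an alpha on a two-sided test of 0.05"). Effect 40 m (11.6: "i.e., a difference of 40m between the two treatment groups"). SD 62 to 72 m (11.6: "Standard deviation of change from baseline between 62 and 72m for the 16-week change in each of the treatment groups"), with 67 m as the central value. 66 subjects per arm, about 9 sites, 2 TRV strata.

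**Assumptions, because the protocol gives no figure.** Site explains 0%, 5%, 10% or 20% of outcome variance. TRV stratum explains 5% (0% in the first case) and baseline 6MW 10%. The minimisation assigns the favoured arm with probability 0.8.

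**The plan's own figure.** A noncentral-t calculation for two means reproduces all nine cells of Table 6, including 60 per arm at SD 67 m and 90% power. 60 × 1.10 = 66 per arm, and 2 × 66 = 132. This point leaves that figure unchanged.

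**Closed form, exact balance.** Let s be the site share of residual variance. The planned model estimates a standard error of σ√(2/66), while the difference actually varies with standard deviation σ√(1−s)·√(2/66). With critical value 1.979:

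- Type I error = P(|Z| > 1.979/√(1−s)). For s = 0.05, 0.10 and 0.20 the bound is 2.030, 2.086 and 2.213, giving 4.2%, 3.7% and 2.7%.
- Relative interval width = 1/√(1−s) = 1.026, 1.054 and 1.118.

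**Simulation of minimisation** (N = 132, SD 67 m; 4000 null runs, 1500 runs at 40 m):

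| Site share | Type I error: planned / with site | 95% CI half-width, m: planned / with site | Width ratio | Power at 40 m: planned / with site |
|---|---|---|---|---|
| 0% | 5.2% / 5.1% | 21.94 / 22.11 | 0.99 | 94.9% / 95.1% |
| 5% | 4.6% / 5.2% | 21.22 / 20.81 | 1.02 | 97.3% / 97.7% |
| 10% | 4.0% / 5.0% | 21.13 / 20.16 | 1.05 | 96.8% / 97.5% |
| 20% | 3.6% / 5.2% | 20.92 / 18.76 | 1.12 | 97.1% / 98.6% |

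The Monte Carlo standard error of a 5% rate is √(0.05 × 0.95/4000) ≈ 0.34 points. Type I errors are nearer nominal than in the closed form, as expected when balance is not exact.

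Power gains in the table are 0.4, 0.7 and 1.5 points. A separate simulation with balance forced within site and TRV gave 93.0 v 93.6%, 93.5 v 94.1% and 94.3 v 96.8%, which are gains of 0.6, 0.6 and 2.5 points. Together this is about 0.5 to 2.5 points.

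Deterministic minimisation (probability 1.0) gave 4.5%, 4.3%, 5.0% and 3.4% for the planned model and 4.7%, 4.6%, 6.1% and 5.4% with site. The 10% pair is high for both models. In every scenario with a site effect, the planned model rejected less often than the model with site.

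**Unstratified Wilcoxon test.** Null rejection with assignment probability 0.8 was 5.6%, 4.2%, 3.9% and 3.0% across the four scenarios.

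**Secondary covariate rule.** A separate null simulation used 5 or 10 candidate covariates of varying assumed prognostic strength, with imbalance thresholds of p < 0.05 or p < 0.20 (all assumed). The treatment test rejected in 1.6% to 5.3% of trials under the rule, against 4.6% to 5.5% for an unadjusted or fully pre-specified model.

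**Degrees of freedom.** Intercept, treatment, baseline 6MW and TRV leave 132 − 4 = 128. Nine sites take 9 − 1 = 8 more, leaving 120.

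**The case against.** The strongest reply is that the only formal test is fully pre-specified and valid, and loses little. Omitting site errs on the safe side, and most of the power differences above are within simulation noise. The loss also requires site to predict change in 6MW. Several features work against that: the endpoint is a within-subject change, baseline 6MW is in the model, and Appendix D asks for a scripted, unencouraged walk with the same tester throughout. A 20% site share is a high-end assumption with no support in the protocol. All of this stands, and it limits the size of the point. It gives no reason to include one minimisation factor and bar the other.

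Four stronger readings are tempting and are not supported:

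- **The primary interval is too wide.** This follows only if site is prognostic. With no site effect, the planned interval is marginally narrower.
- **The log-rank test ignores TRV stratum.** Section 11.2.2 says only "These assessments will utilize log rank tests based on the Kaplan-Meier estimates used to test for differences between the two treatment groups". However, section 11.5.4 states that most secondary efficacy analyses are stratified by TRV, which plausibly covers it, and the accompanying Cox models name TRV stratum. Section 11.5.4 does not fit the single two-sample Wilcoxon test as written.
- **The covariate rule threatens the trial's conclusion or inflates false positives.** It touches only secondary models with descriptive p-values, and in the simulation it pushed rejection rates mainly downwards.
- **One can say how often chance imbalance would trigger the rule.** The protocol gives neither a number of characteristics nor a threshold, so no such probability can be derived from it.

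**Conclusion.** The point holds in a limited form. The primary ANCOVA omits a factor on which allocation is forced to balance, and the protocol wording rules out correcting this in the SAP. For assumed site shares of 5%, 10% and 20%, the cost is a type I error of about 4.6%, 4.0% and 3.6% and an interval about 2%, 5% and 12% wider than necessary, with a small loss of power. These figures rest on the assumed variance shares and the assumed assignment probability. Validity and the sample size are not in question. The Wilcoxon test has the same weakness for both factors, but it is only a sensitivity analysis.

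The secondary covariate rule is a real but descriptive problem: estimates, intervals and p-values will come from a model chosen on the same data, with error rates that can sit well away from nominal. Both are worth changing because the changes are simple and nearly free.

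**What to change.** 1. Add site to the primary ANCOVA alongside baseline 6MW and TRV stratum, pooling small sites by a rule set in advance and applied blind to treatment. Include anticoagulant use if it is added to the minimisation. Amend the closing sentence on covariates in section 11.5.1 to match.
2. Replace the two-sample Wilcoxon test with its TRV-stratified form (van Elteren).
3. Replace the imbalance-and-significance rule for secondary models with a fixed set: the baseline value of the outcome where one exists, TRV stratum and site.

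The cost is a protocol wording change with matching SAP text, and about 8 of 128 residual degrees of freedom. No new data are needed. If site turns out not to matter, the primary interval is about 1% wider (22.11/21.94 = 1.008).
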